### Outcomes

#### Primary feasibility endpoints

Adequate recruitment (defined as ≥ 15% of eligible patients enrolled per center per month to target consistent levels of enrollment) [33]Adequate cold-stored platelet supply (defined as appropriate product available at the time of surgery for ≥ 90% of patients randomized to the delayed cold-stored platelet group).Adequate clinician adherence to randomization assignment (defined as > 90% of all patients being administered the assigned product).

Recruitment and protocol adherence are key common progression criteria for internal pilots of efficient RCTs and ensuring adequate supply of cold-stored platelets is a critical metric for ensuring feasibility of the definitive trial. If all primary feasibility endpoints are met, we will proceed with the larger trial. If 1–2 of 3 feasibility endpoints are met, we will decide if the trial is feasible with modifications to the protocol addressing the specific deficiencies in trial design identified in the pilot. The trial will be considered infeasible if all primary feasibility endpoints fall short of their targets and can not be addressed with modifications to the study protocol. We will hold an investigator meeting to examine the type and number of major deviations, and to define protocol changes required based on the feasibility outcomes.

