### Recruitment

During the surgical preadmission visit, a member of the patient’s circle of care (e.g., surgeon, anesthesiologist, nurse) will invite all elective cardiac surgical patients meeting eligibility criteria to speak with a research coordinator about potential participation in the study. Interested patients will meet with a research coordinator who will provide study information and, where appropriate, obtain written informed consent prior to the scheduled surgical procedure. Thereafter, the research coordinator will contact the hospital blood bank to ensure the availability of adequate supplies of both types of platelets for each patient on the day of surgery (as randomization will only occur on the day of surgery but ABO-identical cold-stored platelets will be prepared a minimum of 24 h prior to the scheduled surgery—see “Randomization/assignment of interventions” section below).

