### Randomization/assignment of interventions

Recruited patients will only be randomized on the day of surgery if the clinical team places an order with the blood bank for platelet transfusion to treat active bleeding during the first 6 h after termination of CPB, and both platelet types are available (Fig. 1). When the platelet order is received, the blood bank technologist or assigned research coordinator will confirm the patient has consented to the study and is enrolled in the trial. The patient will then be randomized and the assigned product will be released [18, 24].

Patients will be randomly assigned (1:1 ratio) to study groups on the day of surgery using a permuted block, stratified (by center) allocation scheme prepared by a biostatistician not involved in the trial. Sequentially numbered sealed envelopes based on the randomization lists will be provided to the blood banks that will be providing the platelet product. This process, which has been successfully used in previous similar studies [25–28], has the advantage of allowing the technologists or coordinators to randomize patients as soon as the order is received without delaying therapy. The spot in the randomization list will not be reused if the patient assigned to it does not receive the platelet product. Once the order for the first platelet product is received and eligibility has been confirmed, the blood bank technologist will open the randomization envelope, and prepare and release the assigned platelet product in tamper-proof, temperature-stable containers that have been validated for this purpose and will be identical for each study arm. To maintain blinding, thermal gloves will be released by the blood bank for product handling and the product label (containing collection and expiration dates and type of platelet) will be obscured.

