### Interventions

Patients randomized to the room temperature platelet (RTP) group will receive ABO-identical, pathogen-reduced via INTERCEPT [29], buffy-coat platelets in platelet additive solution maintained at 22 °C for up to 7 days, as per the current standard of care.

Patients randomized to the delayed cold-stored platelet (DCSP) group will receive up to two doses of ABO-identical, pathogen reduced via INTERCEPT, buffy-coat platelets in platelet additive solution maintained at 22 °C for up to 4 days (with agitation) then placed in cold-storage (at 1–6 °C, without agitation) for a minimum of 24 h, with expiration at 14 days after collection.

The duration of treatment is from the initiation of the first platelet transfusion up to 24 h after CPB or receipt of two doses of the product, whichever occurs first. There will be no other changes to participants’ pre-and post-operative management.

The clinical team will then administer the platelets only if the following criteria are met: [23, 30] (a) bleeding is severe enough to necessitate treatment (Bleeding Severity Scale Moderate or higher [31] or chest tube output ≥ 200 mL/h for any 1 h or ≥ 2 mL/kg/h for 2 consecutive hours in the first 6 postoperative hours [32]; (b) heparin is adequately reversed (confirmed by the return of post-protamine activated clotting time [ACT] to within 15% of baseline ACT); and (c) presence of thrombocytopenia (total platelet count < 100,000 × 10^6^) or platelet dysfunction (functioning platelet count < 75,000 × 10^6^ in response to collagen activation, as measured by the point-of-care platelet function assay PlateletWorks currently in use at both sites). Patients can also be treated irrespective of the platelet count or function if bleeding is deemed to be life-threatening, in accordance with institutional coagulation management algorithms for massive bleeding previously validated by our group [23]. Once the decision is made to administer platelets, the administering clinician will put on the insulated gloves provided, retrieve the product from its sealed temperature-controlled container, carry out routine checks, and administer according to usual care including in-line filtration tubing (170–260 µm) primed with normal saline.

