If a second platelet order is received during the first 24 h after the termination of CPB, the blood bank will prepare and release the correct product (according to group allocation) as per the first unit (in a tamper-proof container along with insulated gloves). To minimize the theoretical thromboembolic risks of cold-stored platelets, if patients require more than two doses of platelets (expected to occur in < 3% of patients, based on data from a recent trial by our group [23]) or require therapy after the 24-h treatment period has elapsed, the blood bank will prepare and release room temperature platelets for both groups. Additional doses of platelets can be administered if there is at least moderate bleeding [31] and other coagulation abnormalities have been addressed as per the standardized coagulation management protocol [23].

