## Discussion

Cold-stored platelets have been extensively studied in preclinical settings, and pilot trials in humans suggest at least comparable efficacy with no increased risk for adverse outcomes compared to room-temperature platelets [9, 18, 24, 39]. However, the safety and efficacy of cold-stored platelets have not been evaluated in large clinical trials and these products are not currently approved for use in Canada. Although they may have hemostatic superiority over conventional room-temperature platelets, there is a possibility that cold-stored platelets may increase the risk of thromboembolic events (as they are hemostatically more activated upon transfusion). However, this risk is largely theoretical and has not been demonstrated in prior studies [18, 40]. Nevertheless, we have taken several steps to minimize this risk and to identify it early should it occur. Additionally, while cohort studies have been published examining the impact on patient care of introducing delayed cold-stored platelets during times of shortages, large studies systematically measuring efficacy and safety are lacking [18].

The co-primary feasibility endpoints are adequate enrollment, adequate cold-stored platelet supply, and adequate clinician adherence to randomization assignment. We selected these outcomes because they will indicate what, if any, are the most important protocol modifications required before undertaking a large, definitive trial. Specifically, recruitment and protocol adherence are key common progression criteria for internal pilots of efficient RCTs [33], and confirming an adequate supply of cold-stored platelets at the time of transfusion is a critical metric for ensuring the feasibility of the definitive trial.

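### The supply progression criterion is scored once, at the time of surgery, so a second cold-stored dose that cannot be supplied within the 24 h window may not count as a supply failure

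*Protocol article*

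**What the plan says.** The Protocol article's section Primary feasibility endpoints defines adequate supply as "appropriate product available at the time of surgery for ≥ 90% of patients randomized to the delayed cold-stored platelet group". The last paragraph of the Background uses the same time point. The Abstract and Determination of sample size mention available product without any time point. The Discussion, explaining the choice of endpoints, says that "confirming an adequate supply of cold-stored platelets at the time of transfusion is a critical metric for ensuring the feasibility of the definitive trial".

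Under Interventions, patients in the DCSP arm "will receive up to two doses of ABO-identical, pathogen reduced via INTERCEPT, buffy-coat platelets in platelet additive solution", and treatment runs "from the initiation of the first platelet transfusion up to 24 h after CPB or receipt of two doses of the product, whichever occurs first". The same section continues: "If a second platelet order is received during the first 24 h after the termination of CPB, the blood bank will prepare and release the" product that matches the allocation.

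Two safeguards act before or at the first order. Under Recruitment, the coordinator contacts the blood bank to "ensure the availability of adequate supplies of both types of platelets for each patient on the day of surgery"; no number of doses is given. Under Randomization/assignment of interventions, a patient is randomized only if platelets are ordered "during the first 6 h after termination of CPB, and both platelet types are available".

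A separate criterion, adherence, requires "> 90% of all patients being administered the assigned product". It is not tied to a dose number. The Statistical analysis section says that point estimates will be compared with the targets to decide on feasibility.

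**The concern.** The criterion looks at one moment, while the treatment it is meant to support extends over a day. Take two DCSP patients. The first receives one cold-stored dose and needs no more. The second receives one cold-stored dose in theatre, has a further order at 10 h, and no ABO-identical, in-date cold-stored unit is left. Read literally, both are supply successes, although supply failed the second patient at the time of transfusion.

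The gap matters because of where the remaining risk lies. Eligibility excludes patients for whom DCSP will not be available, and randomization requires both types to be available at the first order. Among randomized patients, dose one is therefore close to assured. A shortage also cannot be repaired by cooling a unit after the first order: that order comes after bypass ends and the product needs at least 24 h in the cold, so the unit would be ready only when the window had closed.

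Supply is one of three criteria that decide whether the definitive trial goes ahead largely unchanged or is first modified. A shortage that is not scored as supply would not prompt a supply remedy.

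**Working it through.** **1. The plan's own figure.** Determination of sample size states that, with at least 90% of 25 DCSP patients supplied, the lower limit is at least 77.7%. The smallest count meeting 90% of 25 is 23 (23/25 = 92%; 22/25 = 88%). The Agresti-Coull one-sided 95% limit with z = 1.645 (z² = 2.706) is:
- adjusted n = 25 + 2.706 = 27.706
- adjusted p = (23 + 1.353)/27.706 = 0.879
- lower limit = 0.879 − 1.645 × √(0.879 × 0.121/27.706) = 0.777

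The 77.7% is reproduced. The problem lies in the definition, not in the arithmetic.

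**2. Effect at the decision boundary.** Count a patient as supplied only if every study order in the window could be filled.

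| Supplied at surgery | Unfilled second orders among them | Supply as written | Supply over all orders |
|---|---|---|---|
| 23/25 | 1 | 92%, met | 22/25 = 88%, not met (Wilson one-sided 95% lower limit 73.5%) |
| 25/25 | 2 | 100%, met | 23/25 = 92%, met |
| 25/25 | 3 | 100%, met | 22/25 = 88%, not met |

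**3. Would adherence catch it?** Suppose each of three such patients received room-temperature platelets as the second dose, each was counted as non-adherent, and there were no other deviations. Adherence is taken over all 50 patients: (50 − 3)/50 = 94%, which exceeds 90% and is met. Supply over all orders would be 22/25 = 88% and not met. Even if adherence records these cases, its wider denominator can absorb them.

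**4. Sensitivity (assumed inputs).** The article says only that more than two doses are expected in fewer than 3% of patients. It gives neither the share *s* with a second order nor the fraction *f* of those orders that cannot be filled. With availability *a* at surgery, and treating these as independent, the probability that a patient is fully supplied is a × (1 − s × f). The chance of reaching at least 23/25 is then binomial.

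| a | s | f | Fully supplied | P(≥ 23/25), all orders | P(≥ 23/25), as written |
|---|---|---|---|---|---|
| 100% | 10% | 10% | 99% | 0.998 | 1.0 |
| 100% | 30% | 20% | 94% | 0.81 | 1.0 |
| 100% | 50% | 30% | 85% | 0.25 | 1.0 |
| 96% | 10% | 10% | 95% | 0.875 | 0.92 |
| 96% | 20% | 20% | 92% | 0.69 | 0.92 |
| 96% | 30% | 30% | 87% | 0.37 | 0.92 |

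The effect ranges from negligible to decisive, depending on inputs that the article does not supply.

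**The case against.** The best defence is that the second dose is not left unguarded. The coordinator must secure adequate supplies before surgery, and because the course is up to two doses, adequate supplies and appropriate product can be read as covering both. The blood bank is told to release the allocated product on a second order. A room-temperature second dose could count as incorrect product under adherence, could exclude the patient from the per-protocol set as discordant treatment, and could be discussed when the investigators review major deviations. The Discussion sentence is a rationale, not a rival definition. Units kept until 14 days after collection will mostly stay in date for a further day, and DCSP has no routine use in Canada that would drain the stock.

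Much of this stands. A reader might infer that nothing protects or records the second dose; the passages just listed show that this goes too far. A reader might also infer that supply will be overstated by some definite amount, but the article contains no rate from which to compute one. Finally, a reader might infer that product mixing will bias the definitive trial towards non-inferiority. The pilot plans no formal inference on those outcomes, and the argument needs a shortage of unknown size that persists into a trial whose full protocol is not shown.

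What the defence does not remove is the stated time point. Even if two doses are held at surgery, the criterion does not ask whether the second could be supplied when ordered. The adherence route would label a blood-bank shortage as clinician non-adherence, and Primary feasibility endpoints ties protocol changes to the specific deficiency identified.

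**Conclusion.** The concern holds as a flaw in how one progression criterion is defined. The operative wording in the Background and in Primary feasibility endpoints stops at the time of surgery. The treatment window runs to 24 h after bypass, and the Discussion names the time of transfusion. The main supply failure still possible after randomization can therefore score as a success or be attributed to clinicians.

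Its certain size is confined to the boundary: one unfilled second order separates 92% (met) from 88% (not met), and from full supply at surgery it takes three. A miss on this criterion alone would not stop the programme; it would move the decision from proceeding to considering modifications. Anything larger rests on assumed second-order and unfilled rates, and at 10% for each the effect is small. The 77.7% precision statement is sound, and the Abstract and Determination of sample size do not carry the surgery time point. The change is worth making before the criterion is applied, because it is cheap and removes a real ambiguity.

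**What to change.** Reword the endpoint in the Background and in Primary feasibility endpoints along these lines: every study platelet order within 24 h after the end of bypass, up to two per patient, could be filled with ABO-identical, in-date DCSP, for at least 90% of patients randomized to DCSP. Report first-order and second-order fill rates separately, with their denominators, so that a shortage can be located. Reconcile the time point with the Discussion, and attribute a second dose that the blood bank could not supply to supply rather than to clinician adherence alone.

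The denominator stays at 25 patients, so the target and the precision statement are unaffected. No treatment rule changes, and the blood bank already handles each order individually. The cost is a change of wording and a supply percentage that may be slightly less favourable.

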### Eligibility criteria

Adult (≥ 18 years old) patients undergoing elective cardiac surgery with CPB will be eligible for inclusion if they are planning to undergo at least moderately complex surgery *or* have a preoperative platelet count ≤ 150,000 × 10^6^/L (this is a group at high risk of requiring platelet transfusions post-CPB) [2]. Moderately complex index surgery is defined as (i) repair/replacement of more than one valve; (ii) aorta (root/ascending/arch) replacement; (iii) any combination of coronary artery bypass grafting, valve repair/replacement, or aorta (root/ascending/arch) replacement; or (iv) re-do procedures consisting of a repair or revision of a prior cardiac intervention.

Patients will be excluded if DCSP are not going to be available at the time of surgery or if the patient (i) has a congenital or acquired hemostatic disorder (including platelet refractoriness due to anti-platelet and anti-human leukocyte antigen [HLA] antibodies) and/or requires specially matched platelets (including patients with anaphylaxis to blood due to Immunoglobulin A [IgA] deficiency with anti-IgA antibodies), (ii) has known contraindications to heparin, thereby excluding cases where non-reversible anticoagulants (i.e., argatroban) are used, (iii) is on warfarin or direct oral anticoagulants (dabigatran, rivaroxaban, apixaban or edoxaban) within 3 days prior to surgery, (iv) is on antiplatelet drugs within 5 days prior to surgery (excluding acetylsalicylic acid [ASA]), (v) refuses allogeneic blood products, (vi) has a known pregnancy, or (vii) is enrolled in another interventional clinical trial where routine care and management are altered, (vii) is hemodynamically unstable defined as critical care admission or vasopressor or inotrope dependence prior to index surgery, (viii) has a pre-operative requirement for, or expected post-operative dependence upon, mechanical circulatory support (i.e., intra-aortic balloon pump, ventricular assist device).

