### Determination of sample size

This pilot study will include 50 randomized patients, which, accounting for patients who are randomized but not treated and patients who withdraw in both arms, is expected to provide at least 44 evaluable patients, with 22 in each arm. This sample size of 50 patients allows for sufficiently precise estimates of feasibility outcomes [37] in a reasonable timeline. If fewer than 10% (< 5 patients) receive the incorrect product or receive no product, the upper one-sided 95% confidence limit for this percentage will be ≤ 17.3%. In the 25 patients assigned to cold-stored platelets, if at least 90% have product available, the lower confidence limit will be ≥ 77.7%.

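### The platelet supply endpoint is met almost by construction for the first dose, because patients are randomised only when the cold-stored product is already available

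*Protocol article*

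**What the plan says.** Under Primary feasibility endpoints, the Protocol article counts supply as adequate when there is "appropriate product available at the time of surgery for ≥ 90% of patients randomized to the delayed cold-stored platelet group". The Abstract and the end of Background use the same denominator. Determination of sample size plans precision on the 25 patients assigned to DCSP: if at least 90% are supplied, the lower confidence limit is put at 77.7% or more.

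Three other sections govern who reaches that denominator:

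- Randomization/assignment of interventions: a consented patient is randomised, on the day of the operation, only when the blood bank receives a platelet order "to treat active bleeding during the first 6 h after termination of CPB, and both platelet types are available".
- Eligibility criteria: "Patients will be excluded if DCSP are not going to be available at the time of surgery".
- Recruitment: after consent, "the research coordinator will contact the hospital blood bank to ensure the availability of adequate supplies of both types of platelets for each patient".

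Design lists the blood banks' ability to supply ABO-identical DCSP among the things the pilot is to explore. Both Primary feasibility endpoints and the Discussion call supply a critical metric. Under Statistical analysis, point estimates are compared with the targets. If all three endpoints are met, the larger trial goes ahead. If one or two are met, the investigators decide whether a modified trial is feasible. For the last branch, "The trial will be considered infeasible if all primary feasibility endpoints fall short of their targets", with the further condition that protocol changes cannot remedy the shortfalls.

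**The concern.** Availability of DCSP is both the outcome and a condition for entering the denominator. If the blood bank has no suitable DCSP when platelets are ordered, the patient is not randomised and so cannot be recorded as a supply failure. Patients expected in advance to lack the product may be excluded earlier still. Those who remain are, for the first dose, patients already known to have been supplied.

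Two things are at stake. The pilot could report full supply while blood banks often failed to provide the product. And one of the three progression criteria would carry almost no information, so in practice progression would rest on recruitment and adherence.

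**Working it through.** **Inputs.** From the article: 50 randomised 1:1, so 25 to DCSP; target 90%; one-sided 95% limits; about 150 consented; 30–40% of those enrolled expected to receive platelets. Assumed, because the article gives no figure: true DCSP availability *s* at the time of a qualifying order, taken as 70%, 80%, 90% and 95%.

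**1. The article's own figure.** The smallest count reaching 90% of 25 is 23 (23/25 = 92%). The one-sided Agresti–Coull limit with z = 1.645 (z² = 2.706) is:

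- ñ = 25 + 2.706 = 27.706
- p̃ = (23 + 1.353)/27.706 = 0.879
- lower limit = 0.879 − 1.645 × √(0.879 × 0.121/27.706) = 0.777

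This reproduces 77.7% (the exact Clopper–Pearson limit is 76.9%). The arithmetic is sound, but it treats availability among the 25 as free to vary.

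**2. With the randomisation condition.** P(DCSP available | randomised) = 1 for the first dose if the rule is followed. The result is 25/25 at any *s*. The exact lower limit is 0.05^(1/25) = 88.7%.

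**3. What the endpoint could have told us.** Exact binomial chance that the point estimate reaches 90%:

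| Denominator, pass mark | *s* = 70% | 80% | 90% | 95% |
|---|---|---|---|---|
| 25 randomised to DCSP, condition as written | about 100% | about 100% | about 100% | about 100% |
| 25 without the condition, at least 23 | 0.9% | 9.8% | 53.7% | 87.3% |
| 50 qualifying orders, at least 45 | 0.07% | 4.8% | 61.6% | 96.2% |
| 150 consented, at least 135 | under 0.01% | 0.08% | 56.8% | 99.6% |

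For the 150-patient row, *s* is read as day-of-surgery availability.

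**4. Where the failures go.** Randomising 50 takes 50/*s* qualifying orders: about 71 at 70%, 63 at 80% and 56 at 90%. If one consented patient in three has such an order (50/150), that means about 214, 188 and 167 consented patients. None of the three endpoints counts the orders lost for lack of DCSP.

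**5. Precision on other denominators.** Exact one-sided 95% lower limits are 80.1% for 45/50 and 85.0% for 135/150. By the same method 23/25 gives 76.9%. The gain comes mainly from the larger number of patients. The main reason to change the denominator is that supply failures can then be seen.

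**The case against.** Four stronger readings are tempting, and the article does not support any of them.

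- *The endpoint cannot fail.* The intervention allows up to two DCSP doses, and no availability condition is stated for the second. The endpoint does not say that it covers the first dose only. A failure could also follow from randomisation in breach of the rule, or from a unit lost after the envelope is opened. The result is near 100% for the first dose, not fixed at 100%. These routes still do not measure whether the product is there when a patient first needs it.
- *The stop rule can never be reached.* Only the explicit trigger of all three endpoints falling short becomes very unlikely. That branch also requires shortfalls that cannot be remedied. With one or two endpoints met, the investigators may still decide against proceeding, and Statistical analysis allows for a second pilot.
- *The same patients vanish from the recruitment denominator.* This is not established. Recruitment places the blood-bank contact after consent, so shortages found then, or at the time of the order, arise in patients already counted as enrolled. Only patients excluded in advance could leave the eligible pool, and the article does not say when that exclusion is applied.
- *The pilot is blind to any shortage.* Randomisation rates will be assessed by institution. If the 30–40% expected to receive platelets stands for qualifying orders, 70% supply would lower the randomised share to 21–28% (0.7 × 30–40%), which might be noticed. At 90% supply it would be 27–36%, which largely overlaps the expected range. The rate also mixes shortage with patients who needed no platelets, so it does not replace a supply endpoint.

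What survives all four is the conflict between the randomisation condition and the endpoint's denominator. Nothing else in the article resolves it.

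**Conclusion.** The point holds for the first dose. As defined, the supply endpoint is met almost by construction and says little about the blood banks' ability to provide ABO-identical DCSP. At an assumed 80% true supply, a criterion that would be passed 9.8% of the time on 25 unselected patients is passed practically always. The 77.7% limit is correctly calculated, but it describes a quantity that hardly varies under the written rule.

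This rests on the randomisation condition being applied as written. The supply levels are assumptions, and the binomial figures treat patients as independent. The point should be corrected before the pilot is used for a progression decision, because supply is one of only three criteria.

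**What to change.** Leave the randomisation condition as it is and change what is counted.

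1. Redefine the endpoint's denominator as all consented patients with a qualifying platelet order within 6 h of the end of bypass, randomised or not (about 50 or more). Count non-randomisation for lack of ABO-identical DCSP as a failure.
2. As a companion figure, report day-of-surgery availability in all consented patients who reach surgery (about 150).
3. Report separately the otherwise eligible patients excluded before consent because DCSP would not be available. They are not in a consented denominator and cannot be failures within it. State when that exclusion is applied.
4. Report separately the number of second-dose DCSP orders that could not be met.
5. Restate the precision in Determination of sample size on the new denominator, naming the interval method (exact limits: 80.1% at 45/50, 85.0% at 135/150).

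The cost is a change of wording and a short blood-bank availability log. The coordinator already contacts the blood bank for each consented patient. The observed percentage will probably look less favourable than under the present definition.
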